### Participant timeline {13}

Table 1 shows the participant timeline, and Table 2 shows DIUPG Bangladesh programme activities.

**Table 1 Tab1:**
[figure not shown]
Participant timeline: schedule of enrolment, interventions, and assessments

**Table 2 Tab2:** Outline of intervention activities over 20 months of the DIUPG Bangladesh programme

Month 1 to 5	Month 6–10	Month 11–15	Month 16–20
Enterprise and skill development training Asset transfer Health assessment, referrals and rehabilitation and psychosocial support to person with disability One-to-one follow-up and supervision of enterprise and health condition of person with disability Community awareness building Formation of the VSSC Linkage creation	Guidance on asset diversification One-to-one follow-up and supervision of enterprise and health condition of person with disability Community awareness building (i.e. early marriage, dowry, waterborne disease, health and hygiene practise) Ongoing rehabilitation and psychosocial support Savings and payable grant instalment collection Linkage with other services (government and nongovernment) VSSC meeting participation Referral activities	Enterprise and skill development training One-to-one follow-up and supervision of enterprise and health condition of person with disability Ongoing rehabilitation and psychosocial support VSSC meeting participation Referral activities	Formal weekly meetings Payable activities Savings activities One-to-one follow-up and supervision of enterprise and health condition of person with disability Ongoing rehabilitation and psychosocial support Introduction to the regular Microfinance Programme

### Recruitment {15}

BRAC is responsible for the selection of households to take part in the programme. This process is based on household-level indicators, operating across two stages:

Stage 1: Initial screening of potentially eligible households. The programme divides the village population into 5–6 economic groups as previously described where the three poorest groups are shortlisted for selection in DIUPG.

Stage 2: Selection of eligible households. BRAC screens selected households in branch office catchment areas in the target districts. Eligible households are identified based on the eligibility criteria, as earlier described. Verification is completed by the project manager of the DIUPG Bangladesh programme. The project manager verifies that households meet the eligibility criteria, as earlier described.

The unit of participation in the programme is the household; however, a single individual within each household is the ‘project participant’ who is the main recipient of the training and assets. This person is expected to take responsibility for managing the enterprise and participate in other activities, such as training on enterprise management or savings group meetings. Project participants are selected before randomisation.

## Assignment of interventions: allocation

### Sequence generation {16a}

Randomisation for the evaluation of the DIUPG programme is stratified without blocking by district to ensure regional balance. BRAC initially identified 16 districts for intervention implementation. However, for randomisation, two districts were excluded due to delays in their selection process, leaving 14 districts for the evaluation. Specifically, BRAC identified 96 branch office catchment areas (i.e. clusters) across the 14 districts. From these, 72 branch out of 96 office catchment areas were randomly selected through stratified random sampling by district in Stata, due to limited evaluation funding.

### Concealment mechanism {16b}

No concealment mechanism, the random allocation of branches to the treatment and control groups is conducted using Stata.

### Implementation {16c}

The assignment of branch office catchment areas to the intervention and control groups was conducted prior to the baseline survey and programme rollout. This process, carried out by the research team, was designed to align with the programme’s feasibility and evaluation objectives. Within each district, the 72 branch office catchment areas were randomly assigned in a single step to either the treatment or control group, stratified by district and without block randomisation. We included 3 or 6 branch office catchment areas from each district to maintain a 2:1 ratio between the treatment and control groups. In districts where 3 branch office catchment areas were selected, one was randomly assigned to the control arm and the remaining two to the treatment arm. In districts with 6 branch office catchment areas, two were randomly assigned to the control arm and four to the treatment arm.

Randomisation was performed using Stata, ensuring that 24 branch office catchment areas (one-third of the selected branches) were allocated to the control arm, while 48 were assigned to the treatment arm. In the remaining 24 branches not involved in the evaluation, BRAC also implemented DIUPG.

Once randomisation was complete, the baseline survey was conducted, then programme implementation proceeded according to the pre-assigned treatment groups. No reassignment of branches occurred after randomisation. During baseline data collection, neither the enumerators nor the local field staff were aware of which branch offices were assigned to the treatment or control arm.

## Assignment of interventions: blinding

### Who will be blinded {17a}

After households have been allocated to receive the DIUPG Bangladesh programme there is no masking as households and project participants in clusters assigned to intervention or control are aware of their allocation given the nature of the intervention.

### Procedure for unblinding if needed {17b}

Not applicable as there is no post-allocation masking.

## Data collection and management

### Plans for assessment and collection of outcomes {18a}

Baseline data is collected (May–June 2023) after randomisation but before the DIUPG Bangladesh programme starts. After the DIUPG Bangladesh programme ends following 20 months of implementation, endline data is collected (October–November 2025). Data is collected for the baseline and endlines using questionnaires that have been pilot tested. Questionnaires are administered by experienced and trained data collectors, supervised by BIGD, to participants within selected households in both the control and intervention arms. One questionnaire is administered to the individual best able to answer questions about the household (usually the head of the household); a second is administered to the project participant (i.e. the person with disabilities, who in some cases is the same person as the household head). Table 3 displays the key domains for each questionnaire.

**Table 3 Tab3:** Key questionnaire domains

Household questionnaire	Individual questionnaire (if not household head)
Demographics and household characteristics Household welfare and assets Household expenditure Household agriculture, livelihoods, and other income-generating activities Household loans and savings Food security	Self-related health (including assistive device use), health seeking behaviour and psychological wellbeing Social inclusion encompassing: stigma and discrimination, involvement in the community and household decision making; social networks, environmental accessibility)

### Plans to promote participant retention and complete follow-up {18b}

The evaluation will employ standard good practice strategies to promote retention such as collecting multiple contact phone numbers at baseline and making multiple attempts to recontact participants.

### Data management {19}

All data collection for the evaluation is being led by BIGD. Quantitative data, collected through the household surveys, is collected electronically using SurveyCTO where all data is password protected on devices and servers. Data are cleaned and anonymised by BIGD, then shared with LSHTM in the UK using a secure data transfer protocol, where it is securely stored on LSHTM servers.

### Confidentiality {27}

All study staff undergo ethics training and sign a confidentiality agreement. The research team ensures that all research data collected are anonymised using unique identification numbers.

### Plans for collection, laboratory evaluation and storage of biological specimens for genetic or molecular analysis in this trial/future use {33}

Not applicable, as no biological specimens collected.

## Statistical methods

### Statistical methods for primary and secondary outcomes {20a}

We will not use formal hypothesis tests of baseline differences to assess the validity of randomisation, as any observed differences arise by chance under random assignment and do not constitute evidence of imbalance. Baseline characteristics will instead be presented by treatment arm using descriptive statistics (means and standard deviations for continuous variables; counts and proportions for categorical variables). Standardised mean differences will be reported to summarise the magnitude of any baseline differences.

For transparency and descriptive purposes, we will report estimated differences in baseline characteristics between arms using the following regression equation:1$${y}_{ibd}=\alpha +\upbeta {T}_{bd}+{\tau}_{d}+{\varepsilon}_{ibd}$$where $${y}_{ibd}$$ represents the baseline characteristics (primary and secondary outcomes, and some household/individual characteristics such as household size, age, sex of household head, etc.) of the individual or household *i* from branch office *b* in district *d*. $${T}_{bd}$$ is an indicator variable taking the value of 1 if individual or household i is assigned to the treatment group and 0 if assigned to the control group. $${\tau}_{d}$$ are district fixed effects. Since the randomisation is stratified at the district level, we control district fixed effects. $${\varepsilon}_{ibd}$$ is the error term. We will cluster standard error by branch office level, the unit of randomisation. These estimates will be presented for descriptive purposes only and are not assessments of the validity of randomisation.

Programme impacts will be estimated under the intention-to-treat (ITT) principle using the following cross-sectional regression model for continuous outcomes:2$${y}_{ibd}=\alpha +\upbeta {T}_{bd}+{\tau}_{d}+{\varepsilon}_{ibd}$$where $${y}_{ibd}$$ is post-intervention outcome variable (including pre-specified primary and secondary outcomes such as per capita household income, income of persons with disabilities, per capita food consumption and expenditures, and per capita non-food expenditures, etc.); $${T}_{bd}$$ is an indicator variable taking the value of 1 if individual or household i is assigned to the treatment group and 0 if assigned to the control group; $${\tau}_{d}$$ are district fixed effects and $${\varepsilon}_{ibd}$$ are error terms. We will cluster standard error by branch office catchment area level, the unit of randomisation. The key parameter of interest is $$\upbeta$$ which measures the effect of the programme on the outcome variable.

Employment status is a binary outcome and will be analysed using logistic regression, with treatment assignment included as the primary explanatory variable and district fixed effects to account for stratified randomisation. Standard errors will be clustered at the branch office (catchment) level, the unit of randomisation, using cluster-robust estimators. Results will be reported as odds ratios with corresponding confidence intervals and *p*-values.

The primary model specification is fixed and will not be modified based on statistical significance or model fit.

Given five specified primary outcomes, we will control the family-wise type I error rate at two-sided *α* = 0.05 across the primary outcome family using a Bonferroni correction. Accordingly, each primary outcome hypothesis test will be conducted at a two-sided significance level of *α* = 0.01 (0.05/5). We will report effect estimates and confidence intervals for each primary outcome alongside *p*-values; where confidence intervals are used for inference, Bonferroni-adjusted 99% confidence intervals will be reported alongside effect estimates and *p*-values.

Secondary outcomes will be analysed as exploratory. For these outcomes, we report effect estimates, 95% confidence intervals, and nominal two-sided p-values without formal multiplicity adjustment. Secondary findings will not be used to determine overall intervention effectiveness.

Inference is conducted separately for each outcome within the multiplicity-adjusted framework, and interpretation will emphasise effect magnitude and precision rather than binary declarations of overall “success”.

We will additionally report covariate-adjusted models as supplementary analyses. The equation for models with continuous outcomes is:$${y}_{ibd}=\alpha +\beta {T}_{bd}+\gamma {X}_{ibd}+{\tau}_{d}+{\varepsilon}_{ibd}.$$

Here, $${X}_{ibd}$$ is the baseline value of the post-intervention outcome variable, $${y}_{ibd}$$. No additional covariates will be selected. This approach improves statistical precision while preserving the unbiasedness of the treatment effect under random assignment. The same approach will be used for the binary outcome of employment. These adjusted models are interpreted as sensitivity analyses.

Continuous outcomes will be analysed on their natural scale in the primary specification. Where outcomes are substantially right-skewed (e.g. income or expenditure variables), log-transformed models will additionally be reported as robustness analyses. These alternative specifications will be applied consistently across relevant outcomes and reported transparently.

Because assignment may not perfectly determine treatment receipt, the primary model estimates the intention-to-treat (ITT) effect. In the presence of non-compliance, this differs from the effect of actual treatment receipt. As an exploratory analysis, we estimate the local average treatment effect (LATE) using two-stage least squares, with assignment serving as an instrument for treatment receipt.

Due to the 2:1 cluster allocation ratio between the intervention and control arms and variables corresponding to programme exposure, it is not feasible to conduct a blinded analysis of trial data, which represents a limitation of the study.

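### Cluster-robust standard errors with district fixed effects need a stated small-sample correction: with 3 or 6 clusters per district, the usual default runs the 0.01 tests at about 0.022 to 0.026

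*Protocol article*

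**What the plan says.** Section {16c} (Implementation) describes the strata: "We included 3 or 6 branch office catchment areas from each district to maintain a 2:1 ratio". Districts of 3 are split 1 control to 2 treatment, and districts of 6 are split 2 to 4. Section {16a} excludes two districts, "leaving 14 districts for the evaluation". The sample size section gives 72 clusters in total.

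Section {20a} regresses each continuous outcome on treatment and district fixed effects. The reason for the district terms is given with the baseline equation: "Since the randomisation is stratified at the district level, we control district fixed effects". For the impact model it says "We will cluster standard error by branch office catchment area level, the unit of randomisation". For employment, a logistic model with the same terms is used: "Standard errors will be clustered at the branch office (catchment) level, the unit of randomisation, using cluster-robust estimators".

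The error guarantee is a family-wise rate of 0.05 "across the primary outcome family using a Bonferroni correction", so that "each primary outcome hypothesis test will be conducted at a two-sided significance level of" 0.01, with 99% intervals where intervals are used for inference. The section adds: "The primary model specification is fixed and will not be modified based on statistical significance or model fit". It names no finite-sample variance correction, no reference degrees of freedom and no randomisation test.

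**The concern.** Seventy-two clusters look ample for a cluster-robust variance, but the strata are small. Fourteen district effects plus treatment are 15 parameters estimated from 72 clusters, and 12 of those clusters sit in districts of three. The district effects absorb part of the between-cluster variation, so the cluster residuals are systematically too small. The default multiplier in common software hardly compensates, because its parameter count is set against about 2,520 households rather than 72 clusters.

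All five primary outcomes use the same rule. If the default is applied, p-values are too small and intervals too narrow. The shortfall matters most in the far tail, which is where a 0.01 test and a 99% interval operate. Section {20a} also says interpretation will stress magnitude and precision, and precision is what would be overstated.

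**Working it through.** **The plan's own figure.** 0.05/5 = 0.01 is exact. Five independent tests that truly run at 0.01 give 1 − 0.99⁵ = 0.049, within the stated 0.05. The question is whether each test runs at 0.01.

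**Design.** Let *a* be the number of districts with 3 clusters and *b* the number with 6. Then a + b = 14 and 3a + 6b = 72 give a = 4, b = 10, the only solution. The 4 districts of three hold 8 treated and 4 control clusters. The 10 districts of six hold 40 treated and 20 control clusters.

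**Expected variance** (equal cluster sizes, equal error variances).
- Treatment centred within district is w = 1/3 (treated) or −2/3 (control). Σw² = 48 × 1/9 + 24 × 4/9 = 16.
- Cluster leverage is h = 1/(clusters in district) + w²/16. In districts of three this is 0.340 (treated) and 0.361 (control). In districts of six it is 0.174 and 0.194.
- The uncorrected robust variance has expectation Σw²(1 − h)/16 relative to the truth: (0.586 + 1.136 + 3.673 + 7.160)/16 = 12.556/16 = 0.785.
- The usual multiplier is G/(G − 1) × (N − 1)/(N − K) = 72/71 × 2519/2505 = 1.020, so 0.785 × 1.020 = 0.800.
- The standard error is √0.800 = 0.895 of its true value, about 10.5% too small.

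**Size under the null** (400,000 simulated trials at cluster level).

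| Rule | nominal 0.01 | nominal 0.05 |
|---|---|---|
| Usual default (CR1), t with 71 df | 0.0225 | 0.082 |
| Usual default, normal reference | 0.026 | 0.087 |
| CR1, t with 71 df, no district effects | 0.012 | 0.055 |
| CR2, Satterthwaite df 40.7 | 0.010 | 0.050 |

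The third row shows that the small strata cause the excess. Coverage of a nominal 99% interval is 1 − 0.022 = 97.8% down to 1 − 0.026 = 97.4%.

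**Household-level simulation** (mean 35 per cluster, ICC 0.055, t with 71 df, 40,000 trials each, nominal 0.01). Equal cluster sizes give 0.022, a cluster-size coefficient of variation of 0.3 gives 0.025, and 0.5 gives 0.029. Log-normal outcomes give 0.022 to 0.025. At ICC 0 the result is 0.022, so the problem does not depend on the ICC.

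**Employment.** In the linear analogue, the factor 72/71 with a normal reference, as is usual after logit, gives 0.027. A direct logistic simulation gave 0.022 (2,500 trials). Another, assuming 40% employed and ICC 0.055 (20,000 trials), gave 0.028 with that default. In the same trials, a leverage-corrected variance with t on 40.7 df gave 0.010.

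**Family-wise error** (five outcomes, default with t on 71 df). If independent, 1 − (1 − 0.0225)⁵ = 0.108, and simulation also gives 0.108. The simulated values by common correlation are:

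| Correlation | 0 | 0.3 | 0.5 | 0.7 | 0.9 |
|---|---|---|---|---|---|
| Family-wise error | 0.108 | 0.102 | 0.091 | 0.075 | 0.050 |

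**Cost in width.** The 99% critical value is 2.702 on 40.7 df and 2.647 on 71 df. The width ratio is (1/0.895) × (2.702/2.647) = 1.14.

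**The case against.** The strongest reply is that the article does not name the default estimator. CR2 is itself a cluster-robust estimator clustered by branch, so an analyst who used it would comply with section {20a} to the letter. The variant and its degrees of freedom are details often left to an analysis plan, which is not shown here. Stata is named only for sampling and allocation, not for analysis.

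Part of this stands. A reader might infer that the protocol commits to a faulty estimator, and the text does not support that. It does fix the model, the clustering level and the error guarantee together, and the ordinary reading of its wording is the software default. Under that reading the guarantee fails, so naming the rule is more than filling in detail.

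A reader might also infer that the sentence fixing the specification rules out a correction. It does not. It bars changes driven by significance or model fit, and a correction adopted because of the stratum sizes is neither.

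Finally, point estimates and the intention-to-treat estimand are untouched, and section {20a} plays down binary verdicts. That limits the harm, but interval coverage is still wrong under the default.

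**Conclusion.** The concern holds in a conditional form. With the usual default variance, each nominal 0.01 test runs at about 0.022 to 0.026, standard errors are about 10.5% too small, and 99% intervals cover about 97.4% to 97.8%. This follows from the article's own design figures. It assumes equal cluster sizes and error variances; unequal cluster sizes made it worse in simulation.

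The family-wise consequence is less certain. It is tempting to say that the 5% rate becomes about 10%. That needs independent to moderately correlated outcomes, and the article gives no correlation. The supportable statement is about 0.11 at independence and about 0.09 at correlation 0.5, falling to about 0.05 only near 0.9. The per-test inflation and the loss of coverage hold at any correlation.

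**What to change.** Keep the models, the district effects and the odds ratio for employment. Add the variance rule to section {20a}.

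- **Continuous outcomes:** bias-reduced (CR2) cluster-robust standard errors by branch, with Satterthwaite degrees of freedom (about 41 here), for both p-values and 99% intervals.
- **Employment:** the logistic model as planned, with a small-sample-corrected (bias-reduced) cluster-robust variance and a t reference. Support the p-value with a randomisation test that re-draws the actual 2:1 allocation within districts.
- **Linear probability model for employment:** supplementary only, because it would replace the prespecified effect measure.

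State the rule before outcomes are analysed. Trial status says endline data were collected in October–November 2025, and section {20a} says blinded analysis is not feasible, so a rule left open would be chosen by analysts who can see the arms.

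The cost is a few sentences, a few lines of code and intervals about 10% to 15% wider (14% by the arithmetic above). For employment, against a default with a normal reference, it would be nearer 18% if the same degrees of freedom applied: 2.702/2.576 × 1/√0.796 = 1.18.

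### The statement that baseline adjustment improves precision and preserves unbiasedness does not carry over to the employment odds ratio, so the adjusted and unadjusted odds ratios are not a like-for-like sensitivity check

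*Protocol article*

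**What the plan says.** All of this is in the protocol article, Statistical methods for primary and secondary outcomes {20a}.

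- Primary employment model, where the last term in the quote stands for the district indicators: "Employment status is a binary outcome and will be analysed using logistic regression, with treatment assignment included as the primary explanatory variable and district fixed". The measure is fixed: "Results will be reported as odds ratios with corresponding confidence intervals". There is no baseline employment term.
- Supplementary models add one covariate, which "is the baseline value of the post-intervention outcome variable". "No additional covariates will be selected".
- Property claimed for the adjustment: "This approach improves statistical precision while preserving the unbiasedness of the treatment effect under random assignment". It follows an equation labelled as being for continuous outcomes.
- Extension in the next sentence: "The same approach will be used for the binary outcome of employment".
- Role: "These adjusted models are interpreted as sensitivity analyses".
- Emphasis in reporting: "interpretation will emphasise effect magnitude and precision rather than binary declarations of overall" success.

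Employment of persons with disabilities is one of the five primary outcomes (Outcomes {12}). The section does not say that the adjusted OR is a different quantity. It also names no standardised estimate or risk difference for employment.

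**The concern.** In a linear model, the coefficient on randomised treatment means the same thing with or without a baseline covariate, and a predictive covariate shrinks its standard error. A logistic OR has neither property. Conditioning on a strong predictor changes what the OR estimates whenever there is an effect, and it raises the standard error of the log OR.

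The plan nevertheless sets the two ORs side by side as a sensitivity check, after stating that adjustment preserves the effect and adds precision. A reader who takes that at face value could read a gap between them as chance imbalance corrected, or as a stronger programme effect. A wider interval on the log scale would also look like a failed adjustment. Because the plan rests interpretation on magnitude and precision, these are the features most likely to be misread.

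**Working it through.** The protocol states no figure for the employment OR, an employment rate or persistence of employment, so there is nothing to reproduce. The values below are assumptions, except the trial layout.

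**1. Exact calculation, perfect balance.** Model: logit P(employed at endline) = a + log(OR_c)·T + log(OR_b)·X. Here T is arm and X is baseline employment, independent of T. OR_c is the OR given baseline status. The unadjusted OR follows by averaging the probabilities over X and then forming the odds ratio.

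Assume 30% employed at baseline, 30% of controls employed at endline, and OR_b = 10.
- Control: 0.153 if not employed at baseline (odds 0.180) and 0.643 if employed (odds 1.804). Check: 0.3 × 0.643 + 0.7 × 0.153 = 0.300.
- Treated, OR_c = 1.5: odds 0.271 and 2.706, so probabilities 0.213 and 0.730. Average: 0.3 × 0.730 + 0.7 × 0.213 = 0.368.
- Unadjusted OR = (0.368/0.632) / (0.300/0.700) = 1.36. Risk difference = 0.068.
- Treated, OR_c = 2.0: probabilities 0.265 and 0.783, average 0.3 × 0.783 + 0.7 × 0.265 = 0.420. Unadjusted OR = (0.420/0.580) / (0.300/0.700) = 1.69.
- Treated, OR_c = 0.5: odds 0.090 and 0.902, probabilities 0.083 and 0.474, average 0.3 × 0.474 + 0.7 × 0.083 = 0.200. Unadjusted OR = (0.200/0.800) / (0.300/0.700) = 0.58. The adjusted OR is here the smaller number, but again the one further from 1.
- At OR_c = 1 the two coincide.

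**2. Range.** Control employment 20, 30 or 50%; baseline employment 20, 30 or 50%; OR_b 2, 4, 10 or 20:

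| Adjusted OR | Unadjusted OR, lowest to highest |
|---|---|
| 1.50 | 1.28 to 1.49 |
| 2.00 | 1.53 to 1.98 |

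The gap is negligible at OR_b = 2 and widest at OR_b = 20.

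**3. Precision.** Simulation of the trial layout: 72 clusters of 35 households, 48 against 24, 14 districts. Both planned logistic models were fitted with district fixed effects and cluster-robust standard errors. There were 200 replicates per scenario, with 30% baseline and control employment and a between-cluster SD of 0.4 on the logit scale.

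| OR_c | OR_b | OR unadjusted / adjusted | SE of log OR | Mean z |
|---|---|---|---|---|
| 1.5 | 10 | 1.37 / 1.50 | 0.104 / 0.127 | 3.02 / 3.21 |
| 1.5 | 20 | 1.29 / 1.49 | 0.098 / 0.134 | 2.58 / 2.98 |
| 2.0 | 10 | 1.71 / 1.99 | 0.107 / 0.128 | 5.08 / 5.44 |
| 1.0 | 10 | 1.01 / 1.01 | 0.106 / 0.128 | 0.09 / 0.06 |

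In the first row the standard error rises by 22% (0.1269/0.1044). The spread of the log OR across replicates rises too, from 0.119 to 0.141, so this is not an artefact of the robust estimator. The mean z rises as well: the test gains a little even though the standard error grows.

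**4. A common scale removes the gap.** In the first scenario, linear probability models give risk differences of 0.069 unadjusted and 0.068 adjusted, and the standard error falls from 0.0227 to 0.0211 (7%). Standardising the adjusted logistic model gives a risk difference of 0.068 and an OR of 1.36, against 1.37 unadjusted. The spread of the standardised log OR is 0.107, against 0.119 unadjusted. The property that the protocol claims does hold on this scale.

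**The case against.** **Only a supplementary analysis is touched.** This stands. The primary employment model has no baseline term and is declared fixed. Its test at the 0.01 level, its p-value and its 99% interval do not change. A reader might infer that the primary employment result is biased or invalid; the protocol does not support that.

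**The extension may be procedural only.** The unbiasedness sentence follows an equation for continuous outcomes, and the next sentence may mean no more than adding the baseline value for employment too. That reading is possible, but the two ORs are still compared as a sensitivity check with no warning that they estimate different things.

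**The adjusted OR is a sound estimate.** This also stands. It is a valid OR conditional on baseline employment, and its test of no effect is valid and slightly more powerful, so it can still check the presence and direction of an effect. A reader might infer that the adjusted OR is wrong, or always larger. It is further from 1, and equal to the unadjusted OR when there is no effect or baseline employment does not predict endline employment.

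**The gap may be small.** With weak persistence it is negligible. The surveys are more than two years apart, so persistence may be modest. In the first scenario the gap of 0.09 on the log scale (ln 1.496 − ln 1.367) is less than one standard error. It is still systematic rather than sampling noise.

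**Employment may be uncommon.** A reader might add that employment is common, so the OR will be misread as a relative risk. The protocol gives no rate, and index participants include children and people with severe disabilities. The point does not rest on this.

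**Conclusion.** The point holds, as a limited one. The precision and unbiasedness statement is correct for the linear models and incorrect if carried over to the employment OR. The adjusted and unadjusted ORs are different estimands. Strictly, one conditions on district and the other on district plus baseline employment. A gap between them is therefore not evidence of imbalance or of a stronger effect.

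The size depends on assumed values: 20-50% employment, a baseline-endline OR of 2-20, and baseline employment balanced between arms. The gap is nil under no effect and negligible when persistence is weak. At the strong end, an adjusted 2.00 sits beside an unadjusted 1.53. Conclusions from the primary employment test are unaffected.

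**What to change.** 1. Limit the precision and unbiasedness sentence to the linear models for continuous outcomes.
2. Keep the pre-specified odds ratio as the primary measure for employment, from the model already fixed. The endline survey took place before the current protocol version (Trial status), and nothing here calls for replacing that measure.
3. Label the adjusted OR as conditional on baseline employment, and state that it is expected to lie further from 1 than the unadjusted OR when there is an effect and baseline employment is predictive.
4. For the employment sensitivity comparison, add the marginal risk difference, standardised from the unadjusted and the baseline-adjusted logistic models, with cluster-robust standard errors. The two then address the same quantity.

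The cost is some wording, one post-estimation step and one extra reported quantity, which should be labelled as added after endline collection. No new data are needed.
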